### Sample size considerations

We used two years of existing readmissions data to conduct power calculations for the ITS design. This was done using the simulation approach developed by Zhang et al. [39]. We estimated the Mean Squared Error (MSE), baseline intercept, and trend in the pre-intervention period using the pre-intervention data. Further we assumed either moderate or strong autocorrelation (AR(1) = 0.4 or 0.8); a change in intercept of 0, and two-sided α = 5%. We varied the number of post-intervention observation points from 6 to 30 and calculated the required change in slope that can be detected with at least 80% power. The analysis of the pre-intervention data showed strong secular trends in the primary outcome measure. We anticipate that for most outcomes, monthly observations will be used; in the case of small denominators for some outcomes, we may need to use quarterly or semi-annual intervals.

Based on these calculations we will use 36 pre- and post-intervention data points for most outcomes (with a minimum of 6 pre- and post-intervention data points for some secondary outcomes). As each data point for the primary outcome will contain one month’s data this equates to three years of pre-intervention and three years of post-intervention data.

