**Methods/design:**

We are working with local stakeholders to develop CPWs for COPD with the aims of improving care while reducing utilization. The CPWs will employ several steps including: standardizing diagnostic training, unifying components of chronic disease care, coordinating education and reconditioning programs, and ensuring care uses best practices. Further, we have worked to identify evidence-informed implementation strategies which will be tailored to the local context.

We will conduct a three-year research project using an interrupted time series (ITS) design in the form of a multiple baseline approach with control groups. The CPW will be implemented in two health regions (experimental groups) and two health regions will act as controls (control groups). The experimental and control groups will each contain an urban and rural health region. Primary outcomes for the study will be quality of care operationalized using hospital readmission rates and emergency department (ED) presentation rates. Secondary outcomes will be healthcare utilization and guideline adherence, operationalized using hospital admission rates, hospital length of stay and general practitioner (GP) visits. Results will be analyzed using segmented regression analysis.

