## Discussion

Funding for the research has been awarded by the Lung Health Institute of Canada, the Saskatchewan Ministry of Health and through private industry (Novartis). The Research Ethics Board deemed to the project to be exempt from ethics review as the work conducted is a quality improvement project using automatically conducted and de-identified data. The study has been registered through clinicaltrials.gov (NCT03075709). Intervention implementation is expected to begin in RQHR in June 2017 with preliminary meetings with rural stakeholders following. Data collection will conclude 18 months after the start of implementation for each health region.

Successful steps to improve quality of life and reduce healthcare utilization have already been taken in some Saskatchewan health regions; however, these successes have not yet been replicated across the province. This has left substantial disparities in health outcomes for COPD patients among the province’s health regions. We aim to take the first steps to abate these differences by implementing a CPW in two Saskatchewan health regions.

In addition to increasing the quality of care received by COPD patients, this project will also provide evidence on the effects of CPWs in both urban and rural settings. This is crucial to decision making as CPWs have not yet been evaluated within Saskatchewan. Further, the intervention will provide a rigorous evaluation of the use of CPWs to improve care for COPD patients, adding to the limited evidence base currently available. If the pathways are found effective in both urban and rural settings, we will work with all stakeholders to implement similar CPWs across all areas of the province.

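### The sample size section plans 36 monthly post-intervention points for the primary outcome, but the Discussion ends data collection at 18 months in each region, which allows at most 18

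*Protocol article*

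**What the plan says.** Protocol article, Sample size considerations: "we will use 36 pre- and post-intervention data points for most outcomes". Because "each data point for the primary outcome will contain one month’s data", the section concludes that "this equates to three years of pre-intervention and three years of post-intervention data". A minimum of 6 points on each side is allowed for some secondary outcomes. Quarterly or semi-annual intervals are allowed where denominators are small.

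The same section describes the supporting simulation. It used two years of readmissions data, AR(1) of 0.4 or 0.8, "a change in intercept of 0, and two-sided α = 5"%, and solved for the slope change detectable with at least 80% power. On series length it says: "We varied the number of post-intervention observation points from 6 to 30".

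Protocol article, Discussion: "Data collection will conclude 18 months after the start of implementation for each health region". Implementation in the urban region is expected in June 2017. Settings and Discussion place the rural region later; it is to be chosen after implementation in the urban region.

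Protocol article, Abstract, Methods/design: "We will conduct a three-year research project".

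**The concern.** The two statements about the post-intervention period cannot both hold for the primary outcome. The choice matters because the sample size work assumes no change in intercept and targets the change in slope. The precision of a slope change depends strongly on how long the post-intervention segment is.

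The project timeline does not settle the matter. If all data are collected within three years, and the rural region starts after the urban one, 36 post-implementation months cannot fit in both regions. As written, a reader cannot tell when the primary analysis will be run or what slope change it can detect.

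**Working it through.** **Step 1. The plan's own conversion.** 36 monthly points / 12 = 3.0 years. This reproduces. The choice of 36 itself cannot be reproduced, because the article gives neither the mean squared error nor any detectable slope.

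**Step 2. Points available under the Discussion.**
- Monthly: 18 / 1 = 18 points, against 36 planned (50%).
- Whole series: 36 + 18 = 54, against 36 + 36 = 72 (75%).
- Quarterly: 18 / 3 = 6 points, exactly the stated minimum.
- Semi-annual: 18 / 6 = 3 points, below the minimum of 6. Under 36 months it would be 36 / 6 = 6, so this shortfall arises only if 18 months governs.

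**Step 3. Precision of the slope change.** The model is the one in the Analysis section: intercept, pre-slope, level change and slope change. It is fitted to one series with AR(1) errors of known autocorrelation and equal marginal variance. The variance is the slope-change element of (X′V⁻¹X)⁻¹, where V has entries ρ^|i−j|. Standard errors (SE) are in units of the marginal SD per month.

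| Pre + post points | SE, ρ = 0.4 | SE, ρ = 0.8 |
|---|---|---|
| 36 + 36 | 0.0336 | 0.0563 |
| 36 + 30 | 0.0390 | 0.0637 |
| 24 + 30 | 0.0529 | 0.0823 |
| 36 + 18 | 0.0674 | 0.0942 |

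The slope change detectable with 80% power is (1.96 + 0.84) × SE. The unknown mean squared error therefore cancels from a ratio of two designs:
- ρ = 0.4: 0.0674 / 0.0336 ≈ 2.0
- ρ = 0.8: 0.0942 / 0.0563 ≈ 1.67

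**Step 4. Power for a fixed slope.** This needs an assumption the article does not supply, namely the design at which the slope of interest has exactly 80% power. With that design as anchor,

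power at 36+18 = Φ(2.80 × SE(anchor) / SE(36+18) − 1.96).

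| Anchor for 80% power | ρ = 0.4 | ρ = 0.8 |
|---|---|---|
| 36 + 36 (stated design) | Φ(1.398 − 1.96) = 29% | Φ(1.673 − 1.96) = 39% |
| 36 + 30 (longest post period simulated) | Φ(1.62 − 1.96) = 37% | Φ(1.89 − 1.96) = 47% |
| 24 + 30 (two years of pre-data assumed) | Φ(2.20 − 1.96) = 59% | Φ(2.45 − 1.96) = 69% |

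**Step 5. Sensitivity.** With the 36+36 anchor, a simulation (4,000 runs, known autocorrelation) gave 27% and 38% at 36+18. Leaving out the level-change term gave 36% and 41%. Adding an independent control series of equal variance and length changes the absolute standard errors but not the ratio of 36 to 18 post points.

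**The case against.** The strongest reply is that the article does not show the 18-month statement to be the governing one. The sample size section commits to 36 points. Admissions, readmissions, length of stay and GP visits come from existing databases (Data sources), so a later extract is possible. This stands. A reader might infer that half the planned post-intervention data will never be collected, but the text supports only that the two statements conflict.

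A reader might also infer that most of the power is lost. That does not hold in general. The article gives no target slope and no power at 36 points, and the range in step 4 shows how far the answer moves with the anchor.

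Nor does it follow that a null slope result would be uninformative. Eighteen points lie inside the simulated range of 6 to 30, so the authors' own method can give a detectable slope there. Without a target effect, nobody can call that slope inadequate.

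That 36 lies outside the simulated range is a minor reporting matter. With other assumptions unchanged, a slope detectable with 80% power at 36+30 has about 89% to 90% power at 36+36.

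The contradiction survives all of this. The article describes no other data stream to which the 18 months could refer. Nor is this detail left to a fuller document: the article states both figures.

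**Conclusion.** The point holds as an internal contradiction about the primary outcome: 36 monthly post-intervention points in one section, at most 18 in another, with nothing to reconcile them. The three-year project with a later rural start adds to the conflict, on the condition that all data are collected within it.

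The firm measure of size is the ratio of detectable slope changes, about 2.0 (AR 0.4) or 1.7 (AR 0.8), if 18 months governs. It assumes 36 pre-intervention points, a single series, the Analysis section's model and AR(1) errors with the plan's own values. The power figures are illustrations that depend on the assumed anchor. The article needs correcting before it can serve as the reference for the primary analysis.

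**What to change.** Make Sample size considerations, the Discussion and the project length in the Abstract agree, by one of two routes.

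1. **Keep 36 points.** Set the end of data extraction to 36 months after the start of implementation in each region, adjust the stated project length, and report the detectable slope change at 36 points. Where the data are routine administrative records, the cost is mainly time: results come 18 months later than under the Discussion's date.
2. **Keep 18 months.** Change the sample size section to 18 post-intervention points for the primary outcome, restate the slope change detectable with 80% power for AR(1) of 0.4 and 0.8, and drop semi-annual intervals, since the stated minimum of 6 points cannot then be met. The cost is a less favourable detectable effect and a re-run or re-reading of the simulation at a length it already covers.

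Either way, give the number of pre-intervention points used in the simulation and the detectable slope it returned, so that the choice of series length can be checked.

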### Settings

In order to evaluate the interventions, each health region will be matched with a control. For the intervention implemented in the Regina Qu’Appelle Health Region (RQHR), Saskatoon Health Region (SHR) will act as the control. Rural health regions will be chosen following implementation in RQHR and will occur following stakeholder consultation. As with the urban setting, the chosen rural health region will be compared to an appropriate control health region.

### Data sources

Data regarding hospital admissions rates, hospital readmission rate and length of stay will be retrieved through the Discharge Abstracts Database from the Canadian Institute of Health Information (CIHI) [40]. Data regarding scheduled GP visits will be retrieved through the Saskatchewan Health Quality Council Database. Data will be retrieved at the health region level and disaggregated to the hospital level.

## Discussion

Funding for the research has been awarded by the Lung Health Institute of Canada, the Saskatchewan Ministry of Health and through private industry (Novartis). The Research Ethics Board deemed to the project to be exempt from ethics review as the work conducted is a quality improvement project using automatically conducted and de-identified data. The study has been registered through clinicaltrials.gov (NCT03075709). Intervention implementation is expected to begin in RQHR in June 2017 with preliminary meetings with rural stakeholders following. Data collection will conclude 18 months after the start of implementation for each health region.

Successful steps to improve quality of life and reduce healthcare utilization have already been taken in some Saskatchewan health regions; however, these successes have not yet been replicated across the province. This has left substantial disparities in health outcomes for COPD patients among the province’s health regions. We aim to take the first steps to abate these differences by implementing a CPW in two Saskatchewan health regions.

In addition to increasing the quality of care received by COPD patients, this project will also provide evidence on the effects of CPWs in both urban and rural settings. This is crucial to decision making as CPWs have not yet been evaluated within Saskatchewan. Further, the intervention will provide a rigorous evaluation of the use of CPWs to improve care for COPD patients, adding to the limited evidence base currently available. If the pathways are found effective in both urban and rural settings, we will work with all stakeholders to implement similar CPWs across all areas of the province.

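### Ending each region's series 18 months after its own start, not on one common date, shortens the urban pair's view of the later rural start and leaves later urban months unused

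*Protocol article*

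**What the plan says.** The Abstract and the Design section describe an "interrupted time series (ITS) design in the form of a multiple baseline approach with control groups". The starts are staggered. The Discussion states "Intervention implementation is expected to begin in RQHR in June 2017 with preliminary meetings with rural stakeholders following", and Settings adds "Rural health regions will be chosen following implementation in RQHR". No rural start date is given. On comparators, Settings says "In order to evaluate the interventions, each health region will be matched with a control"; the Saskatoon region is the control for Regina Qu'Appelle.

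The end of the series is set in the Discussion: "Data collection will conclude 18 months after the start of implementation for each health region". The cut-off is therefore counted from each region's own start. No common calendar end date appears.

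Sample size considerations gives a different post length: "we will use 36 pre- and post-intervention data points for most outcomes", and for the monthly primary outcome "this equates to three years of pre-intervention and three years of post-intervention data". The Abstract gives the project length: "We will conduct a three-year research project".

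**The concern.** A multiple-baseline design is more convincing than a set of separate before-and-after series because each series can be inspected at the other series' break date. A real effect should appear in each region at its own start and not elsewhere. A province-wide shift or a coding change should appear everywhere at once.

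If the urban series close first, the urban pair gives little or no information on whether a change at the rural break also happened elsewhere. The loss includes the urban control, which receives no pathway in this study and could act as a second untreated series at the rural break.

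Precision is also at stake. The power work set the intercept change to zero and asked what slope change could be detected, and slope precision depends strongly on the number of post-intervention points. The rule stops the urban series while data are still being collected for the rural pair.

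**Working it through.** **Inputs from the protocol article.** Urban start June 2017; 18 post months by the Discussion; 36 monthly pre and 36 monthly post points by Sample size considerations; AR(1) of 0.4 or 0.8, intercept change 0, two-sided 5% and 80% power, also from Sample size considerations.

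**Assumption.** The rural lag L is not stated. Values of 6, 12 and 18 months are shown.

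**The plan's own figures.** 36 monthly points / 12 = 3.0 years, which agrees with Sample size considerations. The Discussion's rule gives 18 monthly points, half of that. The simulated power cannot be reproduced, because the mean squared error, baseline intercept, trend and detectable slope are not reported.

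**Step 1: coverage of the rural start by the urban pair.** With 18 post months the urban series runs from June 2017 to November 2018. Urban months after the rural start = max(0, 18 − L):

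| L | Urban months after the rural start | Urban post points with a common end (18 + L) |
|---|---|---|
| 6 | 12 | 24 |
| 12 | 6 | 30 |
| 18 | 0 | 36 |

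With 36 post months per region, coverage is max(0, 36 − L) = 30, 24 or 18 months.

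**Step 2: coverage of the urban start by the rural pair.** A 36-month rural baseline spans June 2017 for any L from 1 to 35. At L = 12, for example, 24 baseline months fall before the urban start and 12 after it.

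**Step 3: precision of the urban slope change.** The model is one series with intercept, trend, level change and slope change, fitted by generalised least squares with known AR(1) errors and 36 pre points. The ratio is SE(common end) / SE(region-relative end).

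| Post length | L | Points compared | Ratio (SE cut), AR 0.4 | Ratio (SE cut), AR 0.8 |
|---|---|---|---|---|
| 18 | 6 | 24 v 18 | 0.72 (28%) | 0.80 (20%) |
| 18 | 12 | 30 v 18 | 0.58 (42%) | 0.68 (32%) |
| 18 | 18 | 36 v 18 | 0.50 (50%) | 0.60 (40%) |
| 36 | 6 | 42 v 36 | 0.90 (10%) | 0.91 (9%) |
| 36 | 12 | 48 v 36 | 0.84 (16%) | 0.84 (16%) |
| 36 | 18 | 54 v 36 | 0.80 (20%) | 0.79 (21%) |

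Power = Φ(2.80 / ratio − 1.96). As an illustration, take a slope change that has 80% power at 18 post points. With 24 points (L = 6) it has Φ(2.80 / 0.721 − 1.96) = 97% at AR 0.4 and Φ(2.80 / 0.797 − 1.96) = 94% at AR 0.8. The 80% anchor at 18 points is chosen here for illustration; the article reports no detectable slope.

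**Step 4: the check in the untreated urban control.** The same model is fitted to the urban control with a break at the rural start, so there are 36 + L points before it. The SE for a coincident slope shift with 18 − L points after the break is compared with the SE for 18 points. It is 1.7 times (L = 6) or 4.1 times (L = 12) larger at AR 0.4, and 1.4 or 2.7 times larger at AR 0.8. At L = 18 no check is possible. A partial overlap is thus a weaker safeguard than the month count suggests.

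**The case against.** A reader might infer that the urban pair is never observed across the rural start and that the multiple-baseline comparison is lost. The documents do not support this. Non-observation needs L of 18 months or more under the 18-month rule, and no rural date is given. The rural baseline still provides an untreated series at the urban break, and every intervention region keeps a concurrent matched control. That the rural effect has one matched control follows from the pairing in Settings, not from the cut-off.

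A reader might also infer that the harm is the same whatever post length is chosen. It is not. If 36 post months apply, the urban series already reaches 18 months past the rural start for every lag up to 18, and the precision gain from a common end shrinks to about 9–21%. Much of the larger figure comes from the unresolved conflict between 18 and 36 months.

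Three further points deserve weight. Equal follow-up per region is a defensible choice, because it gives urban and rural estimates the same horizon. The final step listed under Aims of the CPWs is to improve on weaknesses found in the evaluation, so late urban months may follow a changed pathway. The extra months cannot be called free: no data costs are stated, and Data sources names no source for emergency department presentations.

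These arguments reduce the size of the point and shape the remedy. They do not explain why a multiple-baseline design should close its series on different dates.

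**Conclusion.** The point holds as an inexpensive improvement to the design, not as a fatal flaw. A region-relative cut-off fits a multiple-baseline design with staggered starts poorly. It weakens the check at the rural break, to 12, 6 or 0 of 18 months at lags of 6, 12 or 18, and leaves L urban months unused. The gain in urban slope precision from using them is 28–50% (AR 0.4) or 20–40% (AR 0.8) with 18 post months, and about 9–21% with 36.

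The size rests on an assumed lag, on a single-series approximation with known autocorrelation rather than the protocol's own simulation, and on which post length is meant. Confidence is moderate for that reason. The disagreement between 18 months in the Discussion and 36 points in Sample size considerations is the firmer defect and has to be settled first.

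**What to change.** 1. Reconcile the 18 months in the Discussion with the 36 post-intervention points in Sample size considerations, and state one post length.
2. Replace the region-relative sentence with one common calendar end date for all four regions, set at the agreed post length after the last start. Each region keeps its own break date.
3. Analyse all four series over that window, so that each pair is observed across the other pair's start.
4. Also report the urban effect at the same post length as the rural one, so that the two horizons are comparable.

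The cost is one sentence and a later data extract for the two urban regions. Admissions, readmissions and length of stay come from a routine discharge database. If the three years are counted from June 2017 (an assumption) and the post length is 18 months, the window fits when 18 + L ≤ 36, that is L ≤ 18. With 36 post months after a later rural start it would not fit, so the project length would need to be part of the reconciliation. The downsides are a later final urban result, and late urban months that may reflect pathway changes made after the evaluation or other local changes.

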## Abbreviations

aeCOPD: Exacerbations of Chronic Obstructive Pulmonary Disease
COPD: Chronic Obstructive Pulmonary Disease
CPW: Clinical Pathway
ED: Emergency Department
GP: General Practicioner
HQC: Saskatchewan Health Quality Council
ITS: Interrupted Time Series
RQHR: Regina Qu’Appelle Health Region
SHR: Saskatoon Health Region
